## Methods

### Study Design and Participants

This is designed as a double-blind, randomized controlled, cross-over study. We aim to recruit 12 healthy young men. Volunteers will be recruited via several advertisement strategies including flyers, global emails to staff and students from Victoria University, and Web-based advertisements.

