### Sample Size and Data Analysis

The sample size is based on our previous work where exercise significantly increased ucOC by approximately 6.5% and insulin sensitivity by approximately 35% during a euglycaemic-hyperinsulinaemic clamp (n=11) [7,12]. As such, we estimate that the sample size needed in this cross-over design (power of 80%, alpha=0.05) is 12 individuals.

Descriptive statistics will be used to describe the volunteers’ characteristics as well as the study measurements. Changes from pre-to-post exercise within each trial and between trials will be analyzed by paired *t*-tests. General linear model analysis of the variance will be use to compare multiple time-points within and between interventions. Multilinear regression model will be used to determine associations between selected measurements. All data will be reported as mean ± standard error of mean and all statistical analyses will be conducted at the 95% level of significance ( *P*≤.05).

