### Randomization and Blinding

At the conclusion of the baseline/screening assessments volunteers will be randomly allocated (block allocation) in a double-blind fashion to determine the order of the treatments (prednisolone or placebo). Randomization will be performed using sealed opaque envelopes. The person responsible for the randomization, the investigators and the participants will not be aware of the intervention (prednisolone or placebo). The code for the randomization will be held by the medical practitioner who will supervise the insulin clamp to allow medical intervention in case of adverse responses during the exercise or insulin clamps.

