The following day (the trial day) participants will attend our laboratory in the morning (7 AM) after an overnight fast for the experimental trial (Figure 1). The participant will lie down on a bed and a cannula will be inserted to the antecubital vein. Then a resting blood sample will be obtained. In addition, a resting muscle biopsy will be obtained from the vastus lateralis, under local anesthesia (Xylocaine 1%), using the percutaneous needle biopsy technique as previously described [12]. Exercise will commence 10 to 20 minutes after the resting muscle biopsy. The high intensity exercise will be performed as previously described and will consist of a 6-minute warm-up at 50% to 60% of peak heart rate followed by 4 × 4-minute intervals at 90% to 95% peak heart rate (HR_peak_) and a 2-minute warm-down at 50% to 60% of peak heart. The high-intensity intervals will be separated by 2 minutes of active recovery consisting of cycling at 50% to 70% of peak intensity [12]. Peak heart rate will be defined as the highest heart rate measured during the incremental test.

After completing the exercise, participants will recover for 3 hours and blood samples will be taken immediately, 30 minutes, 1, 2, and 3 hours post exercise (Figure 1). Then, a 2-hour euglycaemic-hyperinsulinaemic clamp (insulin clamp) will be performed. During the clamp blood samples (∼1-1.5 ml) will be taken every 5 minutes to monitor blood glucose levels. A 10-ml blood sample will be taken every 30 minutes during the clamp (see Figure 1) for the analysis of OC, ucOC, insulin, and other markers of bone formation and resorption (the hormones CTX and procollagen 1 N-terminal propeptide (P1NP)). Blood will be centrifuged (10 min at 3500 rpm, 4°C) and serum and plasma will be immediately stored in aliquots at −80ºc until assayed. In addition, a total of three muscle biopsies from the vastus lateralis will be undertaken in each experimental session. Muscle will be analyzed for insulin signaling proteins, markers of muscle inflammation and atrophy signaling proteins. In total, seven muscle biopsies will be obtained during the study. Four biopsies will be obtained during the first session (−24, baseline and pre and post insulin clamp) and three during the second session (baseline and pre and post insulin clamp).

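### The between-trial paired t-test cannot adjust for period. If a period shift exists it loses power, and it is biased only if the two orders also end unequal

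*Protocol article*

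**What the plan says.** Study Design and Participants sets out the design: "This is designed as a double-blind, randomized controlled, cross-over study". Under Randomization and Blinding, participants are "randomly allocated (block allocation) in a double-blind fashion to determine the order of the treatments". The block size is not given.

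Sample Size and Data Analysis names the tests. The comparison between trials is a paired t-test: "Changes from pre-to-post exercise within each trial and between trials will be analyzed by paired" t-tests. A second method follows: "General linear model analysis of the variance will be use to compare multiple time-points within and between interventions". The terms of that model are not listed.

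The Intervention section and the caption of Figure 1 show that the sessions are not identical. One biopsy and 15 ml of blood are taken 24 hours before the first trial only, and that biopsy serves as the earlier time-point for both trials. The biopsy count reflects this: "Four biopsies will be obtained during the first session", against three in the second. The trials are 1 to 3 weeks apart.

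Outcomes Measurements makes the change in serum ucOC and insulin sensitivity the primary outcomes. Muscle signalling and inflammation markers are secondary.

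**The concern.** In a two-period cross-over, each participant's prednisolone-minus-placebo difference contains the treatment effect plus or minus any period difference, with the sign set by the order received. A paired t-test treats all 12 differences as one sample. A period difference therefore enters the estimated variance and, if the two orders are unequal in number, the estimate as well.

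Here there is a designed difference between sessions. The first session's resting biopsy follows another vastus lateralis biopsy by a day, and the second session's does not. This bears most directly on the muscle markers. Insulin sensitivity is measured by one clamp per session, after exercise, so no within-session baseline can remove a shift between visits.

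At stake are the power of a 12-person trial and, if dropout is uneven, a modest bias in the treatment estimate.

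**Working it through.** **The plan's own figure.** The sample-size statement reads "power of 80%, alpha=0.05) is 12 individuals". The effects it cites are effects of exercise: "exercise significantly increased ucOC by approximately 6.5% and insulin sensitivity by approximately 35" per cent. No prednisolone-placebo difference and no SD of the within-person difference are given, so N = 12 cannot be reproduced, only back-solved. For a two-sided paired t-test at 0.05 (sidedness assumed) with n = 12 and df = 11, 80% power needs a standardised paired difference of 0.889 from the noncentral t distribution. The normal approximation gives (1.960 + 0.842)/√12 = 0.809. If the cited percentages were the target differences, the SD of the difference would be 35/0.889 ≈ 39 points for insulin sensitivity and 6.5/0.889 ≈ 7.3 points for ucOC.

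**Inputs to the check.** The effect is 0.889 (back-solved) and the SD of the paired difference is 1. The period shift π is in units of that SD and is assumed over 0 to 1.

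**Mechanism at 6:6.** The differences are τ + π in one order and τ − π in the other.
- The mean is still τ, so there is no bias.
- The variance that the paired test estimates is inflated on average to 1 + π² × 12/11. For π = 0.5 this is 1.273, an SD of 1.13. For π = 1.0 it is 2.091, an SD of 1.45.
- The true variance of the mean is unchanged, so the test is conservative.

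The adjusted analysis averages the two sequence means and pools the within-sequence variance on n − 2 = 10 df. Its noncentrality is 0.889 × √12 = 3.08, and its power is 79.2% whatever π is.

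**Simulation at 6:6 (200,000 runs per cell).**

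| Shift π (SD) | Paired-t power | Adjusted power | Paired-t type I error |
|---|---|---|---|
| 0 | 80% | 79% | 5.0% |
| 0.25 | 78% | 79% | 4.4% |
| 0.5 | 72% | 79% | 3.0% |
| 0.75 | 62% | 79% | 1.6% |
| 1.0 | 48% | 79% | 0.7% |

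**Bias of the unadjusted estimate.** Bias = π × (n₁ − n₂)/n.
- 6:6 or 5:5: zero.
- 6:5 (one dropout from 6:6): π/11. This is 0.045 SD at π = 0.5 and 0.091 SD at π = 1.0, or about 5% and 10% of 0.889.
- 6:4 (two dropouts, both from one order): π × 2/10 = π/5. This is 0.10 SD and 0.20 SD, or about 11% and 22% of 0.889.

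The period-adjusted estimate stayed at 0.889, within simulation error, in every case.

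**Price of adjusting when π = 0.** Power goes from 80.2% to 79.4% at 6:6, from 75.6% to 74.3% at 6:5, and from 70.7% to 67.7% at 6:4.

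**The case against.** The strongest reply is that nothing in the documents shows that a period shift exists, and much in them works against one. The diet before the first trial is recorded and repeated before the second. The same limits on activity, alcohol and caffeine apply before trial days. Dosing and attendance times are fixed, and the sessions are 1 to 3 weeks apart. At a shift of 0.25 SD the two analyses differ by about one power point, and with no shift the paired test is very slightly better. All of this stands, and it makes the benefit of adjustment conditional.

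Several stronger readings are tempting but not supported:
- A reader might infer that the stated analysis will be biased. Bias needs both a shift and unequal sequences. Block allocation makes near-equal sequences likely, and two losses split across the orders leave 5:5 with no bias.
- A reader might infer a risk of false positives. With balanced sequences the type I error falls below 5%.
- A reader might infer that unequal sequences always cost power. If the bias happens to favour the effect, apparent power can rise: at 6:4 with a 0.25 SD shift the paired test shows 73% against 68% adjusted. That gain comes from a shifted estimate.
- A reader might infer that both primary outcomes are equally exposed. An additive level shift between sessions cancels in the pre-to-post-exercise change in ucOC. Only a period effect on the size of the rise would remain.
- A reader might infer that the general linear model omits period. Its terms are not listed, and a condensed article may leave them to the full plan.

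The last reply does not reach the between-trial test. The article names a paired t-test, and that test cannot carry a period term.

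**Conclusion.** The point holds in conditional form. The named between-trial test cannot adjust for period, although order is randomised and the first session has an extra biopsy by design. If there is a period shift, the paired test is conservative. Relative to the adjusted analysis at 6:6, it loses about 7 power points at 0.5 SD (72% against 79%) and about 31 at 1.0 SD (48% against 79%). At 0.25 SD or below the loss is negligible. The bias after one or two dropouts is at most one fifth of the shift.

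These figures rest on an effect back-solved from N = 12 and on assumed shifts, so they illustrate the mechanism and do not forecast this trial's power. The point applies mainly to insulin sensitivity and the muscle markers. It is worth acting on because the remedy costs almost nothing, not because harm has been shown.

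**What to change.** Replace the between-trial paired t-test with a period-adjusted cross-over analysis. Use a linear mixed model with treatment and period as fixed effects and participant as random. For complete data the equivalent is the two-sequence t-test on the paired differences, with 10 df at n = 12. State that the general linear model for multiple time-points also includes period. The pre-to-post tests within a single trial can stay as they are. Fix the wording before the treatment code is broken, so that the choice of analysis cannot depend on the results.

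The change is to analysis wording only. It costs one degree of freedom: about 1 power point at 6:6 if there is no period effect, and about 1 to 3 points at 6:5 or 6:4.

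### For outcomes sampled at many time-points, a linear mixed model would be safer than the general linear model ANOVA, which can either drop incomplete men or understate the error of the treatment effect, depending on how it is run

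*Protocol article*

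**What the plan says.** Sample Size and Data Analysis names two methods for comparing the trials. Single changes go to t-tests: "Changes from pre-to-post exercise within each trial and between trials will be analyzed by paired" *t*-tests. Repeated measurements go to an analysis of variance: "General linear model analysis of the variance will be use to compare multiple time-points within and between interventions". The article states no data layout, error term or list of the samples that enter the model.

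The Intervention section sets the blood sampling for each trial:
- At rest: "Then a resting blood sample will be obtained".
- In recovery: "blood samples will be taken immediately, 30 minutes, 1, 2, and 3 hours post exercise".
- During the two-hour clamp: "A 10-ml blood sample will be taken every 30 minutes during the clamp".

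The planned size is small. Study Design and Participants says "We aim to recruit 12 healthy young men", and the sample size paragraph gives the same number as the requirement ("power of 80%, alpha=0.05) is 12 individuals"). The article shows no allowance for losses.

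**The concern.** The article does name a method for the time courses, so the question is whether that method suits the schedule. The name covers at least two implementations.

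- **Complete-case repeated measures.** Each man is one row with a column for every trial-by-time cell. A man with any empty cell leaves the analysis, and his other valid samples go with him. Validity then requires that losses be unrelated to treatment and outcome.
- **Long-format linear model with participant as a factor.** Each sample is a row, so incomplete men stay. But treatment changes only between sessions. Without a participant-by-session term, the ten samples of one session count as ten independent pieces of information about treatment, and the standard error of the treatment effect can be too small.

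The first form risks losing men from a 12-man comparison. The second risks a false-positive treatment effect. The ucOC time course is among the data exposed. Outcomes Measurements makes change in serum ucOC a primary outcome without naming a time, so it is open how far the primary result rests on this model.

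**Working it through.** **1. Samples per man.** From the Intervention section: 1 at rest, 5 in recovery and 4 in the clamp (30, 60, 90 and 120 minutes, taking the 3-hour recovery sample as clamp time zero).

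(1 + 5 + 4) × 2 trials = 20 per man, and 20 × 12 = 240 in all. Rest and recovery alone give (1 + 5) × 2 = 12 per man. The single sample taken 24 hours before the first trial is left out; with it the count is 21.

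**2. Complete-case form.** The article gives no loss rate, so the per-sample loss *p* is an assumption, as is independence between samples. Expected complete men = 12 × (1 − *p*)^*m* for *m* samples.

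| *p* | *m* = 20 | *m* = 12 |
|---|---|---|
| 0.5% | 12 × 0.905 = 10.9 | 12 × 0.942 = 11.3 |
| 1% | 12 × 0.818 = 9.8 | 12 × 0.886 = 10.6 |
| 2% | 12 × 0.668 = 8.0 | 12 × 0.785 = 9.4 |
| 3% | 12 × 0.544 = 6.5 | 12 × 0.694 = 8.3 |

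With *m* = 20, the binomial chance of losing at least 4 of 12 men is 2%, 16%, 60% and 87% at these four rates.

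**3. The two layouts on the same data.** In a simulated data set, one sample was removed from each of four men. The complete-case layout kept 8 men and 8 × 20 = 160 values. The long layout kept 12 men and 240 − 4 = 236 values. The complete-case layout therefore discarded 236 − 160 = 76 valid values.

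**4. Scale of losing four men.** The planned 12 cannot be rebuilt. The article gives effects ("exercise significantly increased ucOC by approximately 6.5% and insulin sensitivity by approximately 35"%), but no standard deviation and no prednisolone-versus-placebo difference. Working backwards for a two-sided paired t-test (sidedness assumed), 12 men at 80% power imply a standardized difference of 0.889. At that difference, power is 71% with 10 men and 58% with 8. This illustrates the cost for a paired comparison and is not the power of the ANOVA.

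**5. Long-format form without a session term.** Assume residual SD 0.4 and participant-by-session SD *s* = 0.1, 0.2 or 0.3 (illustrative values), with complete data and no treatment effect.
- Expected mean square for treatment: 0.16 + 10*s*².
- Residual degrees of freedom: 240 − 12 − 19 = 209. Of these, 11 carry the session variation.
- Expected residual mean square: 0.16 + (110/209)*s*².
- Ratios: 0.260/0.165 = 1.57, 0.560/0.181 = 3.09 and 1.060/0.207 = 5.11. A correct test has ratio 1.
- Approximate error rate of a nominal 5% test, P(|Z| > 1.97/√ratio): 12%, 26% and 38%. Simulation of this set-up gave 12%, 27% and 39%.

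This concerns the overall treatment effect. A session shift that is constant over time cancels from the treatment-by-time contrasts.

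**6. Paired t-tests.** These need 2 values per man for clamp insulin sensitivity and 4 for a pre-to-post change in both trials. At *p* = 2%, the expected loss is 12 × (1 − 0.98²) = 0.5 men and 12 × (1 − 0.98⁴) = 0.9 men.

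**The case against.** The strongest objection is that the article nowhere says a man with a missing sample is excluded. A general linear model does not imply it, and layout and missing-sample rules usually sit in the full protocol or analysis plan. That is correct. A reader might infer that one missed sample removes a participant and that a few lost tubes would cost a third of the trial. The documents do not support that inference, for four reasons:
- Deletion follows only from the complete-case form.
- No text puts all 20 samples into one model; separate recovery and clamp analyses fit the wording equally well.
- Pre-to-post and between-trial changes go to paired t-tests, which need 2 to 4 values per man.
- Insulin sensitivity comes from the last 30 minutes of the clamp, so a clamp stopped early loses that value under any model.

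The independence assumption is also open to challenge. A blocked cannula or a withdrawal takes several samples from the same man, so for a given number of lost samples fewer men are affected than the formula implies.

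These objections limit the point without removing it. The long-format reading that saves the men needs a participant-by-session term to give a sound test of treatment, and the article does not name one. The point that remains is about a stated method for which a better alternative costs little.

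**Conclusion.** The point holds conditionally, as a worthwhile improvement. Nothing in the article shows that the trial would lose men or that its primary tests are unsound.

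If the ANOVA is run on complete cases over all samples, 10.9 to 6.5 of 12 men are expected to remain in that analysis at 0.5% to 3% loss per sample. With rest and recovery samples only, the range is 11.3 to 8.3. If it is run in long format without a participant-by-session term, all men remain, but the treatment effect can be tested against too small an error: roughly 12% to 39% false positives instead of 5% under the illustrative variances.

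The loss rates, their independence and the variance components are assumptions, because the documents supply none of them. The single-change paired t-tests fall outside the point.

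**What to change.** In Sample Size and Data Analysis, for outcomes measured at several time-points, replace the general linear model ANOVA with a linear mixed model:
- fixed effects for treatment, time, treatment × time and session (first or second);
- random effects for participant and participant-within-session;
- small-sample degrees of freedom, for example Kenward-Roger with REML;
- all available samples from every randomised man who took a capsule, including men who attend only one session.

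Test the treatment difference as a contrast from this model. The paired t-tests on single changes can stay as they are.

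The cost is one or two sentences and a few lines of code, with no new data. The drawback is that 12 men support only a simple covariance structure. The model also relies on losses being explained by the observed data, and it does not restore an insulin-sensitivity value that was never measured.

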### Screening

Fasting blood test: a blood sample will be collected following an overnight fast. Blood will be analyzed at Austin Health pathology using the standard hospital assay protocols for glucose, HbA1c, insulin, triglyceride, low-density lipoprotein, and high-density lipoprotein.

Body composition: dual-energy x-ray absorptiometry (DXA) will be used to assess total body fat and lean body mass. In addition, the DXA will be used to assess fat mass in the abdominal region as well as bone mineral density to exclude osteoporosis [23,24].

Aerobic power (VO_2peak_) will be assessed during a sign and symptom-limited graded exercise test as we previously described [23]. The exercise will be performed on a cycle ergometer and VO_2_for each 15-second interval will be measured by a gas analyzer that will be calibrated as per the manufacturer’s instructions before each test. Participants will be asked to refrain from physical activity (48 hours), and alcohol and caffeine ingestion (24 hours) prior to the screening session and trial days.

### Randomization and Blinding

At the conclusion of the baseline/screening assessments volunteers will be randomly allocated (block allocation) in a double-blind fashion to determine the order of the treatments (prednisolone or placebo). Randomization will be performed using sealed opaque envelopes. The person responsible for the randomization, the investigators and the participants will not be aware of the intervention (prednisolone or placebo). The code for the randomization will be held by the medical practitioner who will supervise the insulin clamp to allow medical intervention in case of adverse responses during the exercise or insulin clamps.

### Intervention

Volunteers will attend our laboratory twice for the experimental trials (Figure 1). On the day prior to the first trial, participants will be asked to record their daily diet in a food diary, which will then be replicated the day prior to their second trial. The two trials (prednisolone or placebo) will be performed 1 to 3 weeks apart. This ensures that the effect of the single dose of prednisolone is “washed out” [25]. Twenty-four hours prior to the first trial day, and a minimum of 1 week after the VO_2peak_test, a single muscle biopsy and 15 ml of blood will be obtained. To avoid an additional biopsy, data from this resting biopsy will be used as the “24 hour prior” time-point for both the placebo and prednisolone trials. Then, at 7 PM (12 hours before the trial) on the day prior to each experimental trial participants will ingest a 20-mg capsule of prednisolone or placebo orally (Avicel- microcrystalline Cellulose NF PH105) (Figure 1).

The timing of the prednisolone ingestion is based on previously published data on the suppressive effect of acute GC treatment on osteocalcin [20]. The prednisolone dose that will be used in this study is slightly higher compared with the dose used by Nielsen et al [20] (10 mg), but is lower compared with doses used in clinical practice to treat inflammatory conditions (30-70 mg/day). Both the prednisolone and placebo will be purchased from the same pharmacy and look and taste identical. Avicel is widely used as a placebo in a variety of drug trials [26].

The following day (the trial day) participants will attend our laboratory in the morning (7 AM) after an overnight fast for the experimental trial (Figure 1). The participant will lie down on a bed and a cannula will be inserted to the antecubital vein. Then a resting blood sample will be obtained. In addition, a resting muscle biopsy will be obtained from the vastus lateralis, under local anesthesia (Xylocaine 1%), using the percutaneous needle biopsy technique as previously described [12]. Exercise will commence 10 to 20 minutes after the resting muscle biopsy. The high intensity exercise will be performed as previously described and will consist of a 6-minute warm-up at 50% to 60% of peak heart rate followed by 4 × 4-minute intervals at 90% to 95% peak heart rate (HR_peak_) and a 2-minute warm-down at 50% to 60% of peak heart. The high-intensity intervals will be separated by 2 minutes of active recovery consisting of cycling at 50% to 70% of peak intensity [12]. Peak heart rate will be defined as the highest heart rate measured during the incremental test.

After completing the exercise, participants will recover for 3 hours and blood samples will be taken immediately, 30 minutes, 1, 2, and 3 hours post exercise (Figure 1). Then, a 2-hour euglycaemic-hyperinsulinaemic clamp (insulin clamp) will be performed. During the clamp blood samples (∼1-1.5 ml) will be taken every 5 minutes to monitor blood glucose levels. A 10-ml blood sample will be taken every 30 minutes during the clamp (see Figure 1) for the analysis of OC, ucOC, insulin, and other markers of bone formation and resorption (the hormones CTX and procollagen 1 N-terminal propeptide (P1NP)). Blood will be centrifuged (10 min at 3500 rpm, 4°C) and serum and plasma will be immediately stored in aliquots at −80ºc until assayed. In addition, a total of three muscle biopsies from the vastus lateralis will be undertaken in each experimental session. Muscle will be analyzed for insulin signaling proteins, markers of muscle inflammation and atrophy signaling proteins. In total, seven muscle biopsies will be obtained during the study. Four biopsies will be obtained during the first session (−24, baseline and pre and post insulin clamp) and three during the second session (baseline and pre and post insulin clamp).

A euglycemic-hyperinsulinemic clamp (insulin clamp) will be performed as previously reported [12,27,28]. Prior to the insulin clamp a single slow release tablet of potassium chloride (600 mg) will be given to reduce the risk of potassium depletion during the insulin clamp. Venous blood samples, from a heated arm vein, will be collected prior and during each session. Insulin will be infused at 40 mU.m^-2^per minute for 120 minutes generating an elevated, stable insulin concentration in the last 30 minutes of the clamp. Insulin sensitivity will be assessed by the glucose infusion rate (GIR, mg·kg^-1^·min^-1^) during the last 30 minutes of the insulin-stimulated period and the GIR per unit of insulin (M-Value) [29]. During both euglycemic-hyperinsulinemic clamp sessions, exogenous glucose will be variably infused to achieve the target blood glucose of approximately 5 mmol/L for the duration of the clamp.

